## Abstract

**Background:**

The transition to parenthood is a cornerstone event for both parents, potentially leading to relevant changes in lifestyle and behaviour. In women, the metabolic changes during and after pregnancy and the deleterious effects of excessive gestational weight gain and postpartum weight retention have been extensively described. However, there is no full understanding about which specific energy balance related behaviours (EBRB) contribute to unfavourable weight gain and weight retention. Furthermore, information on how transition to parenthood affects men is lacking. Therefore, this study aims to investigate changes in body weight, body composition and EBRB in couples transitioning to parenthood.

**Methods:**

TRANSPARENTS is a multi-centre observational follow-up study that focuses on body weight, body composition and EBRB during the transition to parenthood. Couples (women and men) will be recruited during the first trimester of their first pregnancy. Study visits will occur at four occasions (12 weeks of pregnancy, 6 weeks postpartum, 6 months postpartum and 12 months postpartum). Anthropometrics of the parents and new-borns will be assessed including body weight, height/length, body composition (using bio-electrical impedance analysis and measurement of four skinfold thicknesses (biceps, triceps, subscapular and supraspinal/suprailiac)) and waist and hip circumference. Dietary intake, physical activity, sedentary behaviour, smoking habits, sleeping pattern, fatigue, diet and exercise related partner support, mental health, breastfeeding, contraception use, and socio-demographics will be assessed using a questionnaire. In addition, accelerometry will be used to assess physical activity and sedentary behaviour objectively. Also data from women’s medical record, such as pre-pregnancy weight and pregnancy outcomes, will be included. Multilevel modelling will be used to evaluate maternal and paternal changes in body weight, body composition and EBRB during and after pregnancy (primary outcomes). Multiple linear regression analyses will be performed to identify predictors of changes in body weight, body composition and EBRB. All analyses will be adjusted for possible confounders.

**Discussion:**

TRANSPARENTS is a unique project identifying vulnerable parents and (un)favourable changes in EBRB throughout this potentially critical life period. Provided insights will facilitate the development of effective intervention strategies to help couples towards a healthy transition to parenthood.

**Trial registration:**

Clinicaltrials.gov Identifier: NCT03454958. Registered March 2018.

## Background

The worldwide prevalence of overweight and obesity has increased epidemically during the last decennia [1–3], with the greatest prevalence being observed in upper-middle-income level regions such as North America and Western Europe [4, 5]. In Belgium, about half of the adult population is overweight or obese [6], and prevalence of maternal obesity in Europe reaches 25% [7]. Predictions show that these trends of weight gain are to be continued throughout the next couple of decades [8, 9]. Overweight and obesity are major risk factors for non-communicable diseases such as cardiovascular diseases, type 2 diabetes, musculoskeletal disorders, and a number of cancers, and are estimated to account for 3.4 million deaths per year globally [3, 4, 10, 11]. Next to increased mortality rates, co-morbidities attributable to overweight and obesity cause decreased quality of life as well as a large and still growing economic burden [11, 12]. This highlights the urgency to develop effective strategies for the prevention of overweight and obesity.

Although overweight and obesity are caused by a multitude of factors (i.e., genetic, metabolic), the rapid increase in prevalence suggests that, rather than biological changes, behavioural and environmental influences predominate [13]. Weight gain is typically caused by an energy imbalance between energy consumed and energy expended [3]. It is recognised that this imbalance is due to alterations in energy balance related behaviour (EBRB), namely poor eating behaviour characterized by increased intake of energy-dense foods high in fats and free sugars, decreased physical activity levels, and increasing sedentary lifestyles [3].

It has been argued that specific transitional phases during the lifespan, such as living together, marriage, or pregnancy/having a child may have a strong effect on people’s long-term EBRB and body weight [14]. Identification and thorough understanding of critical periods when people are more likely to gain weight or display unhealthy changes in EBRB could help us to develop more effective intervention programs, focusing on that particular stage of life. In this study we will focus on the transition to parenthood, i.e. having a first child.

Research showed that pregnant women are at substantial risk for excessive gestational and postpartum weight gain and retention [15]. Excessive weight gain during pregnancy increases the risk for gestational diabetes, pregnancy-induced hypertension, large-for-gestational age infants etc. [16–19], whereas higher postpartum weight retention can increase risks in a consecutive pregnancy [20] and lead to lifelong obesity and its related non-communicable diseases [21]. A US study demonstrated that parents gain weight more rapidly than childless women and men [22]. A recent Belgian study showed a mean postnatal weight retention of 3.3 kg, with women retaining up to 16.2 kg of weight six weeks after delivery [23]. Evidence further suggests that increased gestational weight gain (GWG) and postpartum weight retention is more likely for the first pregnancy [20, 24]. A recent review also revealed that pregnancy-related weight gain coheres with increases in fat mass in US women [25].

Increased postpartum body weight is generally caused by a combination of both retention of GWG and alterations in lifestyle due to increased demands related to time, finances, fatigue and child care responsibilities [24, 26, 27]. Healthful EBRBs are associated with reduced risk for excessive GWG [28], and thus, in turn, with reduced risk for excessive postpartum weight retention. Recent reviews [29, 30] emphasize the importance of regular physical activity regarding health during preconception, pregnancy and postpartum. However, parenthood and physical activity are often inversely related [31]. A large prospective study in Australia [32] showed that moderate-to-vigorous physical activity declines during the transition to parenthood in both women and men. Similar results were found in a prospective Canadian study reporting decreases in moderate-to-vigorous physical activity but also in sedentary time, while an increase in light intensity activities was observed [33]. Regarding eating behaviour, most studies seem to focus on pre- and early pregnancy nutrition and its effect on infant outcomes [34]. Although the transition to parenthood may negatively impact healthful eating, studies investigating changes in eating behaviour prospectively are scarce. An Australian study reported no significant changes in diet quality and takeaway-food consumption among women and men having their first child [35]. It should be noted, however, that caloric intake was not studied in this study, so it is not clear whether energy balance was disrupted through excess energy intake. In addition, screening of the literature has taught us that (change in) sedentary behaviour remains understudied during this critical life phase. Although there are some Australian, Canadian and US prospective studies on distinct behaviours, to the best of our knowledge, there are no studies investigating pregnancy-related weight gain from a holistic energy balance perspective, i.e. considering eating, physical activity and sedentary behaviour simultaneously. Besides, Western European research on this topic is lacking. Considering the fact that EBRB is strongly culturally related (e.g. differences in eating or physical activity culture between the US, Australia and Europe), it is important to study changes in body weight, body composition and EBRB along with their determinants among child expecting couples in Western Europe.

Most studies investigating changes in body composition or EBRB during the transition to parenthood focus on women while neglecting their life partners. A recent review [36] revealed that fathers spend less time on moderate-to-vigorous physical activity compared to childless men, especially when they have young children. The same review [36] called for further longitudinal research investigating in detail how the arrival of a child influences physical activity behaviour among fathers. Our review of the available literature revealed that prospective studies investigating body weight and composition, and eating and sedentary behaviour among men transitioning to fatherhood are lacking. Moreover, most weight gain/retention interventions focus on the mother, whereas interventions focusing on the couple while making use of mutual reinforcement, may be more efficacious [33]. Also, if both parents display certain behaviours from early on during the upbringing of their child, it is more likely that children will display similar behaviours during childhood and later life through the principles of parental norms and modelling [37]. Hence, pregnancy should be seen as a window of opportunity to shape healthy EBRB by using a family-centred care approach.

Therefore, the first objective of this study is to investigate both maternal and paternal changes in body weight, body composition and EBRB during the transition to parenthood (i.e. having their first child). A second objective is to investigate socio-demographic and behavioural predictors of changes in both maternal and paternal body weight, body composition and EBRB.

## Methods

### Study setting

TRANSPARENTS is a multi-centre follow-up study in which four Belgian hospitals are involved: University Hospital of Brussels (UZ Brussel), University Hospital of Leuven (UZ Leuven), Jessa Hospital in Hasselt and Hospital Oost-Limburg in Genk. Every year, around 8650 children are born across the four hospitals, of which approximately 45% are firstborn children. Recruitment as well as baseline measurements will take place in the hospitals. Follow-up measurements will take place in the hospitals or at the participants’ homes, depending on their preferences. The protocol of the study and all related documents were reviewed and approved by the Ethics Committees of all the participating hospitals. Written informed consent will be provided by all participants upon entry in the study.

### Recruitment of participants and eligibility criteria

Two researchers will be responsible for recruitment of the participants at the obstetric units of the participating hospitals during the intake visit (around the 8th – 12th week of pregnancy). Each researcher will be assigned two hospitals and will be responsible for the recruitment, baseline measurements and follow-up measurements of the participants from the respective hospitals. To optimise recruitment, posters and flyers will be placed in the waiting rooms of the participating hospitals, encouraging potential participants to visit the study website. The flyers will also be handed over by the nurses/midwives of each obstetric unit to couples expecting their first child, and they will be encouraged to fill in a contact sheet when the researcher is not available for informing potential participants. Couples who left their contact details will be contacted by phone or email, depending on their preference, to provide information and ask them to take part in the study.

Only couples expecting their first child (nulliparous women and childless men) can participate in the study. Because of anthropometric and energy balance related differences between men and women (e.g. different dietary habits, differences in physical activity pattern, etc.) [38], we decided not to include lesbian or homosexual couples, as this would result in a heterogenous “partner group” (i.e. consisting of both men and women). Therefore, only male-female couples and only couples of which both parties are eligible and consent to participate will be included in this study. Dutch speaking participants aged 18 year or older, with any body mass index (BMI) and any socio-economic status can participate. Exclusion criteria for participants are the following: unable or unwilling to give informed consent; suffering from a pathological condition that may influence EBRB (e.g. diabetes), having a significant psychiatric disorder, a recent history of bariatric surgery, pregnant through in vitro fertilisation treatment or with requirements for complex medical diets; unable or not allowed to exercise because of medical or other specific reasons (e.g. bed-rest); having a multiple pregnancy (twin, triplet, etc.).

### Sample size

For the main outcomes of this study – changes in body weight, body composition and EBRB – a relatively small effect size of 0.15 is anticipated, as this was the minimum effect size observed in a previous study in which changes in body weight and EBRB during another critical life period (transition from secondary to tertiary education) were investigated [39].

With a statistical power of 0.8, significance level (α) of 0.05, and taking into account an estimated maximum attrition rate of 75%, a minimum of 248 participants (= 124 couples) will be recruited. The number of participants to be recruited in each participating obstetrics unit will depend on the number of new-borns in the respective hospitals. Taking into account the relative yearly share of new-borns in each hospital, minimum targets for UZ Brussel, UZ Leuven, Jessa Hospital and Hospital Oost-Limburg are set at 34, 35, 26 and 29 couples respectively. The expected duration to reach the total target of 124 couples is four months.

### Timing

Couples will be recruited around week 8–12 of pregnancy. Baseline measurements will take place during the twelfth week of pregnancy. Follow-up measurements will take place at six weeks, six months and one year after delivery (Fig. 1). A range of two to three weeks before or after the theoretic measurement point will be allowed. Baseline measurements will take place in the hospitals before or after the routine pregnancy ultrasound evaluation at week 12 of gestation or during a home visit if this is not possible. Follow-up measurements will take place in the hospitals or at the participants’ homes, depending on their preferences.

**Fig. 1 Fig1:**

Timeline of the TRANSPARENTS observational follow-up study

### Data collection

#### Medical record data

Pre-pregnancy weight will be collected from the electronic medical record at inclusion (T0). Complications during pregnancy (e.g. pregnancy diabetes, pre-eclampsia, hypertension), GWG, method of delivery (spontaneous/vaginal, cesarean section) and new-born birthweight will be collected from the electronic medical record after the delivery.

#### Anthropometrics

Anthropometrics of both parents will be assessed at all four time points (T0-T3) following guidelines of the International Society for the Advancement in Kinanthropometry (ISAK) [40]. Height will be measured using a calibrated SECA wall mounted stadiometer (1 mm accurate scale). Body weight (0.1 kg accurate scale) and body composition (fat mass, fat free mass, muscle mass, bone mass, extra-cellular water, intra-cellular water and organ fat) will be measured using TANITA MC780SMA Bio Impedance Analyzer (BIA). BIA is an inexpensive, rapid, non-invasive and safe method for estimating body composition [25, 41]. BMI will be calculated through dividing body weight (in kg) by squared height (in m). A Harpenden skinfold caliper (0.2 mm accurate scale) will be used to measure skin fold thickness at the biceps, triceps, subscapular and supraspinal sites. Cescorf measuring tape (1 mm accurate scale) will be used to measure waist (at the narrowest part of the waist) and hip circumference (at the largest part of the hip), in order to estimate abdominal and gluteofemoral body fat, respectively. Also new-borns’ anthropometrics will be objectively assessed by the researcher. Therefore, body weight, length, head and upper arm circumferences, and biceps, triceps, subscapular and suprailiac skin folds of the new-born will be measured at T1, T2 and T3. All data will be collected consistently by the same two qualified researchers. Researchers will be trained by a certified ISAK anthropometrist in order to collect data in a standardised way [40]. The training will consist of a theoretical and practical part in which the measurements (incl. landmarks) will be explained and demonstrated. In this training session, the researchers will perform several repeated measurements on the abovementioned body sites on several test subjects under supervision of the certified ISAK trainer. To guarantee reliability between the researchers, a second practical session will be organised to further optimize measurements and minimize inter-rater measurement error.

#### Questionnaires

Questionnaires will be used to collect prospective data across all time points including self-reported body weight and height and EBRB, consisting of weight control behaviour, dietary intake (22-items Food Frequency Questionnaire (FFQ) [42]), physical activity (IPAQ – Dutch version) [43] and context-specific sedentary behaviour (adapted from Busschaert et al. with pregnancy and child-birth related sedentary behaviours such as ‘sitting while breastfeeding’ [44]). Besides these EBRB related questions, the questionnaire will also include other health related factors (smoking habits, sleeping pattern, fatigue), questions to assess social support from the partner for eating and physical activity behaviour (based on the Social support for diet and Social support for exercise questionnaire [45]; adjusted for partner support and translated (independently by two different researchers and afterwards put together) to Dutch), psychological wellbeing (Edinburgh Postnatal Depression Scale (EPDS) and Gotland Male Depression Scale (GMDS)), breastfeeding and contraception use (T1-T3), medical conditions and socio-demographics (age, ethnicity, level of education, employment and marital status). The baseline questionnaire (T0) will include additional retrospective questions about pre-pregnancy body weight, changes in EBRB since pregnancy, smoking habits, sleeping pattern and fatigue since pregnancy and nausea during pregnancy (Pregnancy-Unique Quantification of Emesis/Nausea (PUQE)). A link to the questionnaire will be sent by email to each participant (men and women separately). Participants who do not complete the questionnaires within one week will be reminded up to three times by email or text message.

#### Accelerometry

Tri-axial accelerometers (Actigraph GT3X+) will be used to measure physical activity and sedentary behaviour objectively over a one-week period. The accelerometers will be programmed on a sampling frequency of 30 Hz and downloaded at an epoch of 60 s. Data processing will be done with Actilife software. Time spent sedentary and in light, moderate and vigorous physical activity will be calculated in minutes using Freedson cut-off points [46]. Accelerometers will be handed over to the participants on the day of the anthropometric assessments. Starting from the next day, participants will be asked to wear the devices from waking up until going to bed for seven consecutive days. Participants will be asked to remove the accelerometer while swimming, showering or bathing, as well as to keep an activity log writing down such non-wearing intervals. The accelerometers should be returned per pre-franked post package, which the participants receive together with the accelerometers. A detailed overview of the above measurements, methods and time points is presented in Table 1.

**Table 1 Tab1:** Overview of measurements and used methods

Measurements	Measurement tool (number of measures per occasion)	T0		T1	T2	T3
		Retrosp.	Prosp.			
Anthropometrics (parents)						
Body weight	TANITA Scale (once)		X	X	X	X
Body height	SECA Stadiometer (twice)		X	X	X	X
Self-reported weight and height	Questionnaire	X	X	X	X	X
Body composition	TANITA Bio-electrical Impedance Analyzer (once)		X	X	X	X
Skin folds (biceps, triceps, subscapular and supraspinal)	Harpenden skinfold caliper (twice)		X	X	X	X
Waist circumference	Cescorf measuring tape (twice)		X	X	X	X
Hip circumference	Cescorf measuring tape (twice)		X	X	X	X
Anthropometrics (new-born)						
Body weight	SECA Baby Scale			X	X	X
Length	SECA Measuring board (twice)			X	X	X
Head and upper arm circumferences	Cescorf measuring tape (twice)			X	X	X
Skin folds (biceps, triceps, subscapular and suprailiac)	Harpenden skinfold caliper (twice)			X	X	X
EBRB and other health related factors						
Weight control behaviour	Questionnaire	X	X	X	X	X
Changes in dietary and physical activity behaviour since pregnancy	Questionnaire	X				
Dietary intake	Questionnaire: 22-item FFQ		X	X	X	X
Self-reported physical activity	Questionnaire: IPAQ		X	X	X	X
Context-specific sedentary behaviour	Questionnaire		X	X	X	X
Objective physical activity and sedentary behaviour (7 days)	Accelerometry (Actigraph)		X	X	X	X
Smoking habits	Questionnaire	X	X	X	X	X
Sleeping pattern and fatigue	Questionnaire	X	X	X	X	X
Psychosocial						
Partner support for diet and exercise behaviour	Questionnaire		X	X	X	X
Psychological wellbeing	Questionnaire: EPDS and GMDS		X	X	X	X
Socio-demographics and other sample characteristics						
Breastfeeding and contraception use	Questionnaire			X	X	X
Medical conditions (high blood pressure, high cholesterol, heart and vascular diseases, cancer, sport injuries, depression, chronical fatigue, insomnia)	Questionnaire		X	X	X	X
Emesis/Nausea	Questionnaire: PUQE	X				
Socio-demographics (e.g. age, ethnicity, level of education, employment and marital status)	Questionnaire		X	X	X	X
Pre-pregnancy weight, fertility treatment	Medical Record	X				
Complications during pregnancy (e.g. pregnancy diabetes, pre-eclampsia, hypertension), pregnancy weight gain, way of delivery (natural, cesarean section) and new-born birthweight	Medical Record			X		

*IPAQ* International Physical Activity Questionnaire, *FFQ* Food Frequency Questionnaire, *EPDS* Edinburgh Postnatal Depression Scale, *GMDP* Gotland Male Depression Scale, *PUQE* Pregnancy-Unique Quantification of Emesis/Nausea

### Outcomes

The primary aim of the study is to evaluate maternal and paternal changes in body weight, body composition and EBRB during and after pregnancy up to one year after delivery. Therefore, the primary outcomes are changes in body weight, BMI, body composition (fat mass, fat free mass, muscle mass, bone mass, extra-cellular water, intra-cellular water and organ fat), dietary intake, physical activity and sedentary behaviour. Secondary outcomes are socio-demographics, breastfeeding, partner support for diet and exercise behaviour, psychological wellbeing and new-borns’ anthropometrics.

### Data management

An electronic software program (RedCap software) will be used to enter and store data from the medical records, anthropometrics, and questionnaires.

### Statistical analysis

All statistical analyses will be performed in SPSS 25.0 and R (RStudio version 1.1.383). Prior to the statistical analyses, all data will be screened for outliers and data cleaning will be performed when necessary. Descriptive statistics of the sample will be calculated and drop-out analysis will be conducted, using independent samples *t*-tests for quantitative data and *chi*^*2*^ for qualitative data. Multilevel modelling will be performed to evaluate changes in body weight, body composition and EBRB over time according to gender. Multilevel modelling is particularly well fitted to analyse repeated measures over time in a hierarchical structure (i.e. individuals clustered within couples and clustered within hospitals) including missing values (which are anticipated to be present due to the wide range of variables at different time points we aim to measure) [47]. Multiple linear regression analyses will be performed to identify predictors of changes in body weight, body composition and EBRB. All analyses will be adjusted for possible confounders. *P*-values < 0.05 will be considered as statistically significant.

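### Predictors of change are assigned to multiple linear regression, with no stated account of the couple clustering and missing visits that the plan gives as its reasons for multilevel models

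*Protocol article*

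**What the plan says.** The last paragraph of the Background sets the objective: "A second objective is to investigate socio-demographic and behavioural predictors of changes in both maternal and paternal body weight, body composition and EBRB".

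The Statistical analysis section treats the two objectives differently. For change over time: "Multilevel modelling will be performed to evaluate changes in body weight, body composition and EBRB over time according to gender". It defends that choice as follows: "Multilevel modelling is particularly well fitted to analyse repeated measures over time in a hierarchical structure". It describes the structure as "individuals clustered within couples and clustered within hospitals", and adds "including missing values (which are anticipated to be present due to the wide range of variables at different time points we aim to measure". The next sentence turns to the second objective: "Multiple linear regression analyses will be performed to identify predictors of changes in body weight, body composition and EBRB". The only further provisions are adjustment for possible confounders and a 0.05 threshold. The Methods part of the abstract repeats the same division between the two methods.

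Two other statements bear on this. Under Recruitment of participants and eligibility criteria, "only couples of which both parties are eligible and consent to participate will be included in this study", so every participant enters as one of a pair. Under Sample size, the target of 248 participants (124 couples) allows for "an estimated maximum attrition rate of 75"%.

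**The concern.** Both reasons given for the multilevel model apply equally to the predictor analysis, which uses the same couples, outcomes and visits. Multiple linear regression as usually understood assumes independent errors and uses only complete records. Two things are at stake.

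- **Precision of the tests.** If mothers and fathers are in one regression, partners count as independent. Predictors that the couple shares, such as delivery mode, breastfeeding or marital status, then get standard errors that are too small and are flagged too often.
- **Who is analysed.** A change score exists only for people seen at both visits. Partial follow-up is discarded, and the results can depend on who stayed.

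The Discussion intends these results to show who is most at risk and to guide family-based interventions, so false or selective predictors would carry forward.

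**Working it through.** **Inputs from the article.** 248 participants in 124 couples (cluster size 2), four visits, effect size 0.15, power 0.80, alpha 0.05, maximum attrition 75%. The article gives no correlation between partners' changes; rho = 0.2, 0.3 and 0.5 are assumptions.

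**The plan's own figure.** A repeated-measures F test with f = 0.15, four measurements, and an assumed within-person correlation of 0.5 with sphericity needs N = 62 (power 0.801). Then 62 / (1 − 0.75) = 248, as stated. Read this way, the calculation addresses change over time and includes neither partner correlation nor the predictor regressions.

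**Clustering, if the sexes are pooled.** With clusters of two, the variance of a coefficient differs from its ordinary least-squares value by the factor 1 + r_x × rho, where r_x is the correlation of the predictor between partners. For a predictor shared by the couple, r_x = 1:

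- understatement of the standard error = 1 − 1/√(1 + rho)
- true type I error = 2 × [1 − Φ(1.96/√(1 + rho))]

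| rho (assumed) | Variance factor | SE understated by | Type I error |
|---|---|---|---|
| 0.2 | 1.2 | 9% | 7.4% |
| 0.3 | 1.3 | 12% | 8.6% |
| 0.5 | 1.5 | 18% | 11.0% |

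Simulated pooled regressions with 31 or 124 couples agree: about 8.5% to 8.6% at rho = 0.3 and 11.4% at rho = 0.5.

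Other kinds of predictor behave differently:

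- r_x = 0: factor 1; simulated error stays near 5% (4.6% to 5.2%).
- r_x = 0.3: simulated error 5.0% to 6.9% for rho from 0.1 to 0.5.
- A pure within-couple contrast such as sex (r_x = −1): factor 1 − rho; type I error 2.8%, 1.9% and 0.6% at rho = 0.2, 0.3 and 0.5, so the test is conservative.

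**Missing visits.** At the maximum attrition, a change from baseline to the last visit exists for 248 × 0.25 = 62 people, or 31 of each sex if loss is even. Someone seen at six weeks and six months but not at one year contributes nothing to that regression, whereas a multilevel model uses those visits. A multilevel model also remains valid when loss depends on earlier observed outcomes; a complete-case regression of change scores generally does not.

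**The case against.** **The sexes may not be pooled.** This is the strongest objection. The objective speaks of maternal and paternal change. Same-sex couples are excluded because men and women differ in build and behaviour, and some measures, such as nausea and gestational weight gain, are maternal only. Separate fits are a natural reading, and under them the type I error figures above no longer apply. This stands as a limit on the clustering part. However, the article does not state a split for the regression; it attaches gender only to the multilevel model. A split also leaves the hospital level and the loss of partial follow-up untouched.

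**Most candidate predictors are individual-level.** Age, education, diet, activity and sleep differ between partners, so the tabulated inflation is an upper case. This stands. A reader might also infer that standard errors are too large for every predictor that differs within a couple. That is not so: it requires a negative correlation between partners, as for sex.

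**Small numbers come from attrition.** A reader might blame the regression for poor power. With r = tanh[(1.96 + 0.84)/√(n − 3)], the correlation detectable with 80% power is about 0.35 at n = 62 and 0.48 at n = 31. These figures follow mainly from worst-case attrition, for which the article gives no breakdown by visit. A multilevel model recovers only part of the loss, because it cannot supply last-visit outcomes that were never observed.

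**An analysis plan may add detail.** Clustered errors or imputation could be specified there, and a drop-out analysis is planned. But the article does more than stay silent: it names a method for this objective directly after explaining why the data need another. The drop-out analysis describes selective loss and does not correct for it.

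**Conclusion.** The point holds as an inconsistency in a stated method. The plan explains why these data need a multilevel model and then assigns its second objective to a method with no stated account of couples or missing visits.

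The size depends on two things that the article does not fix. The type I error of about 7.4% to 11.0% applies only if women and men are pooled, the predictor is shared by the couple, and the partner correlation is 0.2 to 0.5. For predictors uncorrelated between partners it is about nil. The loss of partial follow-up applies whether or not the sexes are pooled; 62 of 248 is the extreme case, at the last visit under maximum attrition.

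A reader might go on to infer that the sample size is wrong or that the primary analysis is compromised. The article supports neither: 248 reproduces as a calculation for change over time, and the primary change analysis already uses the multilevel model. This should be fixed, but it does not undermine the study's main objective.

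**What to change.** Replace the regression sentence with the multilevel model already planned. Enter each predictor with its interaction with time, and with gender where mothers and fathers are compared. Keep the couple and individual levels and use all observed outcome visits. The baseline outcome is then part of the response and no change score is needed. Where the predictor is itself a changing behaviour, enter it as time-varying, since a simple predictor-by-time term does not represent it.

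If regression is kept, state that it is fitted separately by sex or with couple-clustered standard errors, and that missing visits and predictors are handled by multiple imputation.

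The cost is a sentence or two of text and a little more modelling work, with the same software and data. Interactions add parameters, so three-way terms should be kept to the comparisons that need them. The change does not recover unobserved last-visit outcomes. A multilevel model by default also drops records with missing predictors, so those need a stated method either way.
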